## Abstract

**Background:**

Frozen shoulder (FS) is a musculoskeletal condition of poorly understood etiology that results in shoulder pain and large mobility deficits. Despite some physical therapy interventions, such as joint mobilization and exercise, having shown therapeutic benefit, a definitive treatment does not currently exist. The aim of this study will be to compare the effectiveness of a central nervous system (CNS)-directed treatment program versus a standard medical and physical therapy care program on outcomes in participants with FS.

**Methods/design:**

The study is a two-group, randomized clinical trial with blinding of participants and assessors. Participants will be recruited via referrals from orthopedic surgeons and physical therapists, community-based advertisements, private care practices and hospitals. Participants will be randomized to receive either a CNS-focused treatment program or standard medical and physical therapy care. The Shoulder Pain And Disability Index (SPADI) will be the primary outcome, while the Numeric Pain Rating Scale (NPRS), shoulder range of movement (ROM), The Patient Specific Functional Scale, two-point discrimination threshold and laterality judgement accuracy will be the secondary outcomes. Assessment will occur at baseline, at the end of the treatment program (week 10), and at 3 and 6 months’ follow-up.

**Discussion:**

Preliminary data suggest that treatments that target CNS function are a promising approach to the treatment of people with shoulder pain including patients with FS. In the context of modest effects from most available physical therapy treatments for FS, this CNS-focused approach may lead to improved clinical outcomes. The trial should determine if the CNS-directed program is more effective than traditional interventions at reducing pain intensity and improving function in a FS cohort and will follow up participants for 6 months, providing important information on the persistence of any treatment effects.

**Trial registration:**

NCT03320200. Registered on October 25, 2017.

**Electronic supplementary material:**

The online version of this article (10.1186/s13063-019-3585-z) contains supplementary material, which is available to authorized users.

## Key points

The effects of central nervous system (CNS) treatment on frozen shoulder will be analyzedGraded sensory discrimination and Graded Motor Imagery trainings will be appliedOutcome measures will be shoulder pain and disability

## Background

Frozen shoulder (FS) is a musculoskeletal condition of poorly understood etiology that results in shoulder pain and large mobility deficits [1]. Obtaining pain relief and improving shoulder function are of significant concern to people with FS. Unfortunately, a definitive treatment for this condition does not currently exist and there is little consensus as to what constitutes optimal evidence-based treatment [2]. Despite some physical therapy interventions, such as joint mobilization and exercise, having shown therapeutic benefit [3–5], there is little evidence to suggest that the disease prognosis is affected [6]. Other interventions, such as guided intra-articular corticosteroid injections, appear to show more promising outcomes in the short-term than stand-alone physical therapy interventions [7]. Evidence also suggests the injection benefit being enhanced both in the short term and medium term when combined with physical therapy [8]. The current state of evidence for the various physical therapy treatments suggest that further and alternative approaches for managing FS might be investigated [6].

There is preliminary evidence from two systematic reviews showing that central pain processing mechanisms can contribute to the pain experience in a subgroup of patients with shoulder pain of different etiologies, including those with chronic subacromial impingement syndrome and post-stroke shoulder pain [9, 10]. Similarly, it could be argued that continuous nociceptive barrage, as in the early stages of FS, could lead to peripheral and subsequently long-lasting central sensitization. However, up to now the involvement of central mechanisms in FS remains speculative [6]. Interventions, such as pain neuroscience education and Graded Motor Imagery (GMI), which are thought to target the CNS, have been developed and tested in people with chronic musculoskeletal disorders with some promising results [11–15]. To our knowledge, only two case-series studies have used a CNS-focused treatment program in people with shoulder pain [16, 17]. In one study, a brief mirror therapy intervention resulted in statistically significant improvements in pain, pain catastrophization, fear avoidance and shoulder flexion active range of motion (ROM) in patients presenting with shoulder pain and limited active motion [16]. However, only 8.7% of the studied sample was diagnosed with FS and immediate post-intervention effects were solely assessed. In a second case series, Louw et al. showed that a sensory discrimination task applied to 55 patients with shoulder pain and limited ROM (including FS) resulted in an immediate increase of shoulder ROM (*p* = 0.001) with 25 patients (40%) meeting or exceeding minimal detectable change, but the study failed to report on the specific number of patients with FS [17]. Despite the positive effects shown in these two case series, the potential benefits of adding other approaches addressing the CNS (e.g., sensory discrimination training) remains largely unknown. Hence, further investigation of these preliminary findings in adequately powered randomized controlled trials together with exploration of the longer-term effects of centrally focused interventions for people with FS, is needed.

The aim of this study is to compare the effectiveness of a CNS-directed treatment program versus a standard medical and physical therapy care program on outcomes in participants with FS.

## Methods

### Design

This is a two-group, randomized clinical trial with blinding of participants and assessors.

### Setting

Participants will be recruited via referrals from orthopedic surgeons and physical therapists, community-based advertisements, private care practices and hospitals in Valencia, Spain. Potential referrals will be informed of the trial and the referral process via formal meetings and trial information sheets. This study is reported in line with the Standard Protocol Items; Recommendations for Interventional Trials (SPIRIT) Statement [18] (Additional file 1).

### Participants

Participants will be screened to determine whether they meet the following inclusion and exclusion criteria:

#### Inclusion criteria

Primary or idiopathic FS, defined as FS not associated with a systemic condition or history of injury [19]; greater than 50% reduction in passive external rotation when compared to the uninvolved shoulder or less than 30° of external rotation [20]; range of motion loss of greater than 25% in at least two movement planes in comparison to the uninvolved shoulder [20]; pain and restricted movement present for at least 1 month reaching a plateau or worsening [20]; normal shoulder x-rays (with the exception of osteopenia of the humeral head and calcific tendinosis) [21].

#### Exclusion criteria

Locked dislocations, rheumatic disease, fractures or avascular necrosis on radiographs; surgery in the upper quadrant region < 12 months prior to the study; skin or medical conditions that prevent patients from receiving tactile stimuli on the shoulder; neurological or motor disorders including a diagnosis of dyslexia or difficulty performing a rapid naming task; visual and mental health conditions that preclude successful participation.

### Details of the interventions

Participants will be randomized to receive either a CNS-focused treatment program or.

standard medical and physical therapy care. Adherence to both interventions will be monitored using an individual treatment diary where the time of day and duration of each clinic and home session will be recorded [22]. Adverse events will be recorded through passive capture. Patients will be requested to not participate in other treatments for their shoulder during the 10-week study period and any change in medication type or dosage during the study period will be recorded.

Trial physical therapists performing both interventions will have worked in private or public practice for at least 2 years. The clinicians performing the CNS-focused treatment will be engaged in a 1-day training session led by the author ([name]) for specific training in delivery of the interverventions comprising the program. This training session will include group discussions and quarterly workshops to review specific cases in the context of the CNS-focused treatment program. In addition, these physical therapists will be provided with a treatment manual outlining the CNS-focused treatment protocol and the details of each intervention included in the protocol. In order to ensure a good level of proficiency with the treatment protocol, trial physical therapists will go through a theoretical test and a practical exam with questions and techniques included in the protocol. The interventions are described in detail according to Template for Intervention Description and Replication (TIDieR) Checklist recommendations [23].

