### CNS-focused treatment program

Participants randomized to this treatment will receive a CNS-focused intervention consisting of a 10-session treatment program delivered as 60-min sessions, scheduled once a week, over a period of 10 weeks. All treatment sessions are one-on-one. In addition, participants will complete a home treatment program entailing 30 min of training, five times per week that finishes at session 10. The intervention includes discussion of the participant’s shoulder pain experience from a pain neuroscience perspective (e.g., pain neuroscience education) [24], graded sensory discrimination training and GMI training. These interventions are likely to overlap due to variable allocation of time to each of the treatments within the clinic and home treatment sessions.

Prior to training, participants will be given an explanation of the proposed treatment and the aim of the study. Patients will be shown a picture of the “brain map” (homunculus) and taught how the map becomes “less sharp” when people are in pain, since the affected shoulder is not being moved [16]. They will be told that when the map is sharpened, it may help to reduce not only their pain but also their mobility [16]. By using sensory discrimination training and GMI, the therapy aims to sharpen the map of the shoulder in the brain and thus improve pain and movement.

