### Standard medical and physical therapy care program

Participants randomized to standard medical and physical therapy care will receive a 10-session treatment program of the same duration as the CNS-focused treatment. This standard treatment will include one corticosteroid infiltration provided in the early acute stage followed by a multimodal physical therapy program including analgesic modalities (e.g., TENS, cryotherapy) and exercise and manual therapy techniques addressing the specific mobility deficits of each patient [31]. Physical therapists will be instructed not to include interventions that were similar to those used in the group receiving the CNS-focused protocol (e.g., using mirrors or imagined movements) and to include a home program that involves a training load comparable to that in the other group.

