### Blinding

Participants will be blinded to both study hypothesis and group allocation. It will not be possible to blind the treating physical therapists who are responsable of performing the interventions. All the assessments will be conducted by researchers who will be blinded to group allocation. Statitistical analysis will be performed by a statistician blinded to the study aims.

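### Passive capture is the only stated way of recording adverse events; with arms that differ in content and unblinded therapists, harms may be under-counted and counted unequally

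*Protocol article*

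**What the plan says.** The Protocol article, *Details of the interventions*, deals with harms in one sentence: "Adverse events will be recorded through passive capture". It names no recorder, question or checklist. Adverse events are not among the outcomes listed in *Primary and secondary outcome measures and assessment points*.

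The same section sets up an instrument that could carry a question: "Adherence to both interventions will be monitored using an individual treatment diary". Its stated content is the time and length of clinic and home sessions. Changes in medication are also recorded.

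Contact during treatment is matched. The CNS-focused arm has a "10-session treatment program delivered as 60-min sessions, scheduled once a week, over a period of 10 weeks", and the standard-care arm "will receive a 10-session treatment program of the same duration as the CNS-focused treatment".

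The content is not matched. Standard care includes "one corticosteroid infiltration provided in the early acute stage", then analgesic modalities, exercise and manual therapy. The section on Graded Motor Imagery training contains a rule to review the training if symptoms stay worse, and advice to stop if mirror therapy increases pain. No such text appears for standard care.

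On blinding: "It will not be possible to blind the treating physical therapists", while "All the assessments will be conducted by researchers who will be blinded to group allocation".

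**The concern.** Under passive capture, a count depends on what a participant thinks worth mentioning and on what someone else notices. Two things can follow.

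First, events may be lost, above all those arising in unsupervised home training (30 minutes, five times a week in the CNS-focused arm, with a comparable load asked for in standard care).

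Second, the share recorded may differ by arm. An injection and manual therapy may prompt different reports from an imagery and touch programme. The written worsening rule, and the case-review workshops described for the CNS clinicians only, may draw attention to symptoms in the other arm. Which way any imbalance would run cannot be told.

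At stake is the usefulness of the descriptive harms record. *Significance and implications for practice* hopes the results could change how frozen shoulder is managed, and readers will then want to know what happened to patients in each arm. Events lost at collection cannot be recovered in the analysis.

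**Working it through.** The plan has no harms figure to reproduce. The one planned number used here is 17 per group, from *Sample size calculations*, taken as stated. The planned pilot of 20 may change it.

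**Inputs not in the document (assumed).** True risk of an event per participant, p: 10% or 20%. Share of affected participants recorded, c: 25% to 100%.

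**Formulas.** Expected number of participants with a recorded event in an arm = 17 × p × c. Chance that an arm records none = (1 − p × c)^17.

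**Same capture in both arms, p = 20%:**

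| Capture c | Expected recorded | Chance of recording none |
|---|---|---|
| 100% | 17 × 0.20 × 1.00 = 3.4 | 0.80^17 = 0.023 |
| 75% | 17 × 0.20 × 0.75 = 2.55 | 0.85^17 = 0.063 |
| 50% | 17 × 0.20 × 0.50 = 1.7 | 0.90^17 = 0.167 |
| 25% | 17 × 0.20 × 0.25 = 0.85 | 0.95^17 = 0.418 |

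**A rarer event, p = 10%.** The chance of recording at least one in an arm is 1 − 0.90^17 = 0.83 with full capture, 1 − 0.95^17 = 0.58 at 50%, and 1 − 0.97^17 = 0.40 at 30%.

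**Different capture by arm.** The table applies one capture share to both arms, so it says nothing about imbalance. Take p = 20% in both arms, with capture of 30% in one and 60% in the other:
- 17 × 0.20 × 0.30 = 1.02 recorded
- 17 × 0.20 × 0.60 = 2.04 recorded

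That is a twofold gap from recording alone. The 30% and 60% are chosen only to show the mechanism.

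**What full capture could deliver.** If an arm of 17 had no events, all fully ascertained, the one-sided 95% upper limit for the true risk would be 1 − 0.05^(1/17) = 0.16. Even perfect collection would not support a claim of equal safety.

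**The case against.** The strongest reply is that this is a condensed article. Recorder, form and prompts are commonly left to the full protocol, which *Ethics and dissemination* says will be made available. That is right for the missing detail, and none of it is held against the plan here. It does not cover the method itself, which the article fixes in words.

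A reader might draw four stronger conclusions that the document does not support:

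- **That events pass through unblinded therapists.** No recorder is named. Blinded researchers see every participant at week 10, 3 months and 6 months. The therapists' knowledge of allocation is a possible route to unequal recording, not a stated one.
- **That nothing prompts a report after week 10.** *Recruitment procedures* provides for regular researcher contact by email and telephone, extending to the follow-up sessions. Its stated purpose is adherence, but a participant could still volunteer an event.
- **That harms will be under-counted.** With no event rate or capture share given, this is a risk and not a result. Nor does the injection bias the count by itself. It makes the expected events differ, and bias arises only if reporting differs too.
- **That a planned safety comparison is spoiled.** The stated aim is effectiveness, no safety comparison is planned, and 17 per arm could not carry one.

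There are also partial safeguards. Session number and length are matched, pain is measured at every assessment in both arms, and medication changes are recorded. These narrow the gap, but they do not replace asking every participant the same question.

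**Conclusion.** The point holds as a minor design weakness with a cheap remedy. Passive capture is the only stated method. Given the differing content of the arms and the unblinded therapists, harms may be under-counted and may be counted unequally. Neither the amount nor the direction can be derived from the document. The figures above rest wholly on assumed risks and capture shares, and show only that in arms of 17 a modest loss can leave very few events, or none, on record. The primary SPADI comparison is not affected.

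**What to change.** Replace passive capture with one open question on adverse events, worded identically in both arms and answered by the participant:

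- at each session, as a line in the existing treatment diary;
- at week 10 and at the 3- and 6-month visits, on a short self-completed form, collected after the outcome measures and not shown to the blinded assessor.

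Report the number of events and the number of participants with at least one event, by arm, descriptively and without a claim of comparative safety.

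The cost is one diary line and one form, with no extra visits and no change to treatment. There are two downsides. More minor events will be recorded. There is also a small risk of unblinding, since an answer may mention the injection or manual therapy; that is why the form is self-completed and withheld from the assessor, not asked aloud.

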### CNS-focused treatment program

Participants randomized to this treatment will receive a CNS-focused intervention consisting of a 10-session treatment program delivered as 60-min sessions, scheduled once a week, over a period of 10 weeks. All treatment sessions are one-on-one. In addition, participants will complete a home treatment program entailing 30 min of training, five times per week that finishes at session 10. The intervention includes discussion of the participant’s shoulder pain experience from a pain neuroscience perspective (e.g., pain neuroscience education) [24], graded sensory discrimination training and GMI training. These interventions are likely to overlap due to variable allocation of time to each of the treatments within the clinic and home treatment sessions.

Prior to training, participants will be given an explanation of the proposed treatment and the aim of the study. Patients will be shown a picture of the “brain map” (homunculus) and taught how the map becomes “less sharp” when people are in pain, since the affected shoulder is not being moved [16]. They will be told that when the map is sharpened, it may help to reduce not only their pain but also their mobility [16]. By using sensory discrimination training and GMI, the therapy aims to sharpen the map of the shoulder in the brain and thus improve pain and movement.

#### Graded sensory discrimination training

A graded sensory discrimination training program based on previous work by Wand et al. [13] will be implemented. In this model, participants undertake a training regimen that involves discrimination of stimulus type and location and graphesthesia training in five different stages, graded according to level of theoretical cortical engagement and complexity. Each stage is planned to last a minimum of 2 weeks (10 weeks in total), but can be extended by some days if participants appear not to have sufficiently mastered that stage.

For tactile discrimination training in the first stage (weeks 0–2), participants will be seated in a comfortable position with a mirror between their upper limbs. Evidence has shown that tactile acuity is enhanced with visualization of the reflected image of the unaffected limb (that is, patients look towards the stimulated body part and can see the skin of the opposite body part in the mirror) [25]. Therefore, during the first week of training at home and in the clinic, participants will be positioned so that they can see the reflection of their unaffected arm in a mirror while the affected arm is stimulated. The limbs will be positioned in such a way that the reflected image of the opposite arm is in line with the stimulated arm. Visual feedback will be withdrawn after the first week and will not be used again in any part of the sensory training program.

In this first stage, only localization of the stimulus will be trained. Participants will be shown a digital standard photograph of the shoulder on which nine numbered grids will be marked. The spacing of the grids will be based on the current normative data pertaining to two-point discrimination of the affected joint (e.g., (45.9 mm ± 18.4 mm) [26]. For the shoulder localization blocks, the superior border will be set as 1 cm proximal to the acromioclavicular joint and the lower border reaching the deltoid insertion. While the participant views the photograph and nine-block grids, they will be taught via tactile stimulus with the back of the blunt end of a pencil, where each block is in relation to their shoulder, thus familiarizing them with the nine-block grid [13, 27]. After the familiarization period, the therapist, using a random number sequence, will press lightly on a particular point with the blunt end of a pencil for about 2 s. Pressure will be kept to a minimum to avoid pain provocation. Participants will be instructed to refer to the picture and to indicate which grid has been stimulated. With a correct identification of the area, the therapist will proceed to the next block for identification. If the participants make an error, they will be told which grid (number) has in fact been stimulated, and then the actual position of the grid that they have incorrectly indicated will be stimulated. This in essence will help the participant to develop a greater ability to identify the stimulated grid. Three blocks of 60 stimuli with an interstimulus interval of 15 s and a 3-min rest period between blocks will be used during the treatment session.

At the first session, participants will be accompanied by someone who can assist them to undertake training at home. This assistant will be trained in the task and participants will be advised to undertake 15 min of training at home in addition to the clinic session. Participants will be given a photograph of a standard shoulder on which the stimulation points will be marked and several sets of 60 random number sequences to use for training at home. If at the end of the second week (first stage), for participants who have less than 80% accuracy with one test block of 60 stimuli, the training will be extended for an additional week.

In the next stage (weeks 2–4), participants will be asked to discern both the localization of the stimulus (i.e., the corresponding number on the photograph) and the size of the probe used (type of stimulus). The experimental setup will be similar to that used in the first stage, but this time a probe with a sharp end (pen cap) and a blunt end (cork) will be used. A random number table will be used to randomize both position and probe size. Participants initially will be shown a picture with nine numbered grids marked on the shoulder; the number of grids will be increased to 12 in the second week of this stage. Again, participants will be given feedback about each error they make. Three blocks of 60 stimuli with an interstimulus interval of 15 s and a 3-min rest period between blocks will be used during the treatment session.

Should participants be less than 80% accurate with one test block of 60 stimuli at the end of the second week of this stage, then the training will be extended for an additional week. For home training in this second stage, participants will be given a photograph of the shoulder with the stimulation points and a wine cork and a pen lid to use as stimulus type. They will be given five lists of random combinations of numbers (1–9 or 1–12) and stimuli (cork or pen lid), and will be advised to use a different list each day. Participants will be advised to undertake 15 min of training at home in addition to the clinic session.

The next three stages (weeks 4–10) will involve graphesthesia tasks of increasing difficulty. In this third stage, participants will have to simply recognize letters drawn on the shoulder. Several random sequences of 60 letters will be generated, and three lots of 60 letters will be used in each treatment session with a interstimulus interval of 15 s and a 3-min rest period between blocks. Initially, uppercase letters will be drawn on the shoulder by the therapist with his index finger. Participants will be asked to indicate the letter drawn; if they guessed incorrectly, they will be told the actual letter that has been drawn, and then the letter that they have incorrectly indicated will be re-drawn. Progression within this 2-week block will be undertaken by decreasing the size of the letters, altering the orientation of the letters, and altering the speed at which the letters are drawn. Again, this stage may be extended by 1 week if participants are less than 80% accurate with a test block at the end of 2 weeks. Participants will be advised to undertake 15 min of graphesthesia training at home by using several random sequences of letters.

The next 2-week stage (weeks 6–8) will involve the recognition of three-letter words drawn on the shoulder. The protocol and progression will be almost identical to those outlined for the single-letter task, including the criterion for advancement to the next stage. One additional progression in the last 2 weeks (weeks 8–10) will involve overlapping the letters of the word such that they are all drawn on the same part of the shoulder. Again, this stage can be extended for an additional week if participants were less than 80% accurate at the end of 2 weeks. Participants will be advised to undertake 15 min of graphesthesia training at home by using several random sequences of letters.

A full description of the graded sensory discrimination training program is provided in Table 1.

**Table 1 Tab1:** Summary of progressions used for the graded sensory discrimination training program

Stage	Sensory discrimination training
1 (weeks 0–2)	*Localization training* Determine site of stimulus With visual feedback during first week Without visual feedback during second week
2 (weeks 2–4)	*Localization and stimulus type* Determine site of stimulus Determine size of probe Progress by adding points
3 (weeks 4–6)	*Graphesthesia training* Recognize letters Progress by size Progress by orientation Progress by speed of drawing
4 (weeks 6–8)	*Graphesthesia training* Recognize 3-letter words Progress by size Progress by orientation Progress by speed of drawing Progress by overlapping letters
5 (weeks 8–10)	*Graphesthesia training* Progress by size Progress by orientation Progress by speed of drawing Progress by overlapping numbers

